## Abstract

**Background:**

Tobacco use is presently responsible for the death of over seven million people across the world. In Qatar, it is one of the main causes of premature deaths and preventable diseases. To reduce tobacco use, Qatar has ratified the World Health Organization (WHO)’s Framework Convention on Tobacco Control (FCTC) and has implemented many tobacco-control initiatives. In spite of these measures, tobacco use is still considered a public health threat in Qatar. Pharmacists practicing in retail/community pharmacy settings are often the first port of call for individuals requiring general health advice. Evidence has proven that they have a pivotal role in health promotion and disease prevention including tobacco cessation. However, pharmacists in Qatar are not actively involved in tobacco control and many have not received any education or training about smoking cessation counseling in the past. In an effort to build the capacity of pharmacists towards tobacco control in Qatar, the aim of the proposed study is to design, implement, and evaluate an intensive education program on tobacco dependence treatment for pharmacists in Qatar.

**Methods/design:**

The study will be a prospective randomized controlled trial comparing an intensive tobacco-related education program versus non-tobacco-related training on pharmacists’ tobacco-use-related knowledge, attitudes, self-efficacy, and skills. Community pharmacists practicing in Qatar will be eligible for participation in the study. A random sample of pharmacists will be selected for participation. Consenting participants will be randomly allocated to intervention or control groups. Participants in the intervention group will receive an intensive education program delivered by a multi-disciplinary group of educators, researchers, and clinicians with expertise in tobacco cessation. A short didactic session on a non-tobacco-related topic will be delivered to pharmacists in the control group. The study has two primary outcomes: post-intervention tobacco-related knowledge and post-intervention skills for tobacco cessation assessed using a multiple-choice-based evaluation instrument and an Objective Structured Clinical Examination (OSCE), respectively. The secondary study outcomes are post-intervention attitudes towards tobacco cessation and self-efficacy in tobacco-cessation interventions assessed using a survey instrument. An additional secondary study outcome is the post-intervention performance difference in relation to tobacco-cessation skills in the practice setting assessed using the simulated client approach.

**Discussion:**

If demonstrated to be effective, this education program will be considered as a model that Qatar and the Middle East region can apply to overcome the burden of tobacco-use disorder.

**Trial registration:**

ClinicalTrials.gov, ID: NCT03518476. Registered on 8 May 2018. Version 1/22 June 2018.

**Electronic supplementary material:**

The online version of this article (10.1186/s13063-018-3068-7) contains supplementary material, which is available to authorized users.

## Background

Tobacco use is one of the leading causes of premature morbidity and mortality in the world causing over seven million deaths a year [1]. With the current trend, it is projected that tobacco use will cause more than eight million deaths per year by 2030 [2]. Tobacco-use cessation entails many short- and long-term health benefits for the user, the healthcare system, and to society [3]. These benefits include, but are not limited to, reduced risk of lung cancer and other types of cancers, cardiovascular diseases, and lung diseases such as chronic obstructive pulmonary disease [4]. Despite this, tobacco-use cessation is challenging and difficult to achieve without the support of a healthcare professional. Tobacco-cessation interventions offered by healthcare professionals are more effective in comparison with self-help [5]. Pharmacists practicing in community pharmacies are among the most accessible healthcare professionals by the public for providing advice on health and self-care. Evidence has proven that pharmacists have a pivotal role in health promotion and disease prevention including tobacco-cessation interventions [6, 7]. Indeed with the emergence of the pharmaceutical care concept more than two decades ago, the focus of pharmacists has shifted from product-oriented practice to patient-centered care [8]. Many pharmacists, worldwide, have started applying behavioral interventions to improve health outcomes [6]. In addition, prescription and over-the-counter pharmacotherapies for smoking cessation are readily available in community and retail pharmacies. Nicotine replacement therapy (NRT) is an example of an over-the-counter smoking cessation aid available in most countries including Qatar. Prescription smoking cessation medications include bupropion and varenicline. The availability of these medications provides pharmacists with an opportunity to help patients quit smoking and to combat tobacco use in the community [9]. Pharmacist-delivered tobacco-cessation interventions have been described in the literature [9–15]. For example, Saba et al. have conducted a meta-analysis of the effectiveness of pharmacist-delivered smoking cessation interventions within community pharmacy. The analysis has demonstrated that community pharmacy-based smoking cessation interventions can improve smoking abstinence rates [9].

The International Pharmaceutical Federation (FIP) issued a policy statement in relation to the pharmacist’s role in reducing tobacco use in the community [16]. The U.S. Department of Health and Human Service clinical practice guidelines for treating tobacco use and dependence include strategies to assist clinicians in delivering tobacco-cessation interventions [5]. Furthermore, healthcare providers, including pharmacists, were highly endorsed for delivering tobacco-cessation services in the American Society of Health-System Pharmacists’ (ASHP) Therapeutic Position Statement on the Cessation of Tobacco Use [17].

Tobacco use is a major preventable cause of mortality and morbidity in Qatar. As per the 2013 Global Adult Tobacco Survey (GATS), 12.1% of adults and 20.2% of men smoke tobacco, and 55.4% of smokers smoke an average of 16 cigarettes per day [18]. Moreover, according to the 2013 Global Youth Tobacco Survey (GYTS), 15.7% of school students in Qatar within the age range of 13 and 15 years currently use tobacco [19]. Tobacco-induced diseases including cardiovascular diseases (CVDs) are highly prevalent in Qatar. The mortality rate from CVDs from 2011 to 2013 was 8.3 per 100,000 for Qatari males aged 20–44 years [20]. Furthermore, lung cancer is one of the main causes of cancer-related mortality in males accounting for 17.4% of cancer-related deaths in 2014 [21]. Qatar residents purchase at least one billion cigarettes annually and 150 million dollars are spent per year to cover the hospital fees for smoking-related diseases [22]. To reduce the use of tobacco, Qatar has ratified the World Health Organization (WHO)’s Framework Convention on Tobacco Control (FCTC) [23] and has implemented several initiatives to reduce tobacco use including banning all forms of tobacco advertisement in media, prohibiting smoking in enclosed public areas, forbidding the sale of cigarettes to children under the age of 18 years, introducing graphic/pictorial health warnings on cigarette packs, and others [23, 24]. Despite these initiatives, tobacco use is considered a public health threat in Qatar. Qatar pharmacists and other healthcare providers have excellent opportunities to reduce tobacco use in the country. Currently, Qatar has over 1000 practicing community pharmacists and smoking cessation aids including NRT and varenicline are available over-the-counter in community pharmacies in Qatar [25]. Despite this, published studies have shown that community pharmacists in Qatar are not actively contributing to tobacco control [26]. Only 21% of community pharmacists in Qatar always or most of the time ask patients about their tobacco use or smoking status and less than 50% always or most of the time provide counseling to the purchasers of NRT. Furthermore, 89% of the community pharmacists reported that they did not receive any kind of education or training about smoking cessation counseling in the past. However, 85% of the pharmacists were interested in receiving additional training related to smoking cessation competencies/skills including initiating discussions with patients about smoking, assessing patients’ nicotine dependence, counseling patients using cognitive behavioral techniques, and other topics [26].

To be competent in providing tobacco-cessation interventions and to offer effective tobacco-cessation programs, pharmacists should have the necessary competence, skills, and confidence in relation to tobacco cessation. Several educational interventions were designed and implemented to enhance the knowledge and skills of healthcare professionals in relation to tobacco cessation [27]. Yet the majority of these interventions were implemented and assessed outside the Middle East (ME) region and did not target pharmacists. In addition, these interventions were only delivered by one group of professionals (e.g., nurses, physicians, or pharmacists) with expertise in smoking cessation programs. In an effort to build the capacity of pharmacists on tobacco-use treatment, the aim of this study is to design, implement, and evaluate an intensive education program on tobacco treatment for pharmacists in Qatar. We hypothesize that pharmacists who participate in the program will have better knowledge, attitudes, perceived self-efficacy and skills in relation to tobacco-use treatment than pharmacists who receive no such program (control group).

### Study objectives

The aim of this randomized controlled study is to design, implement, and evaluate an intensive education program provided by team of health professional educators on tobacco-use treatment for pharmacists in Qatar.

The primary objectives of the study are to assess the effectiveness of the program on pharmacists’ knowledge and skills in relation to tobacco and tobacco cessation assessed using a multiple-choice-based evaluation instrument and an Objective Structured Clinical Examination (OSCE), respectively. The secondary objectives are to assess the effectiveness of the program on pharmacists’ attitudes toward tobacco cessation and perceived self-efficacy (i.e.. confidence) in tobacco-cessation interventions, assessed using a survey instrument, and to assess the effectiveness of the program on pharmacists’ tobacco-cessation skills in the practice setting, assessed using the simulated client approach.

## Methods/design

### Study design

The study is a prospective randomized controlled trial comparing the effectiveness of the education program, versus non-tobacco-related training, on pharmacists’ tobacco-related knowledge, attitudes, self-efficacy, and skills. The study methodology and procedures are shown in Fig. 1. The protocol is developed in accordance with the Standard Protocol Items: Recommendations for Interventional Trials guidelines (SPIRIT; Fig. 2 and Additional file 1).

**Fig. 1 Fig1:**
[figure not shown]
A flow chart of the study methodology and processes

**Fig. 2 Fig2:**
[figure not shown]
Standard Protocol Items: Recommendations for Interventional Trials (SPIRIT) diagram

The evaluation of the effectiveness of the program will be conducted using multiple strategies as follows:Assessment of pharmacists’ knowledge, attitudes, and self-efficacy before and after the training programAssessment of pharmacists’ skills using an authentic method (i.e., an OSCE) directly after the completion of the training programAssessment of pharmacists’ skills in the practice setting 3 to 6 months post training program using a simulated client approach

### Study-eligible participants

All community pharmacists practicing in Qatar are eligible for participation in the study. There are no specific exclusion criteria for participants’ enrollment in the study.

### Recruitment of participants and randomization

Information about the study and its purpose were made available to the Ministry of Public Health, which subsequently made available a database that has contact details of all community pharmacists practicing in the country (around 1000 pharmacists). A stratified random sample of 200 pharmacists was obtained from the list. Stratification was done by pharmacy so that no more than one pharmacist from each pharmacy would participate. Invitations to participate in the study will be made by the study research assistants (RAs) over the phone or in writing. Those who express interest will be sent a Participant Information Sheet (PIS) and a consent form. Consenting participants will be randomly allocated to intervention or control groups using permuted block randomization with blocks of size 2, 4, and 6. Randomization will be made by the study statistician who is not involved in the recruitment of the pharmacist and will be concealed for the RAs recruiting the pharmacists. Blinding of study participants in relation to their allocation to the study groups will not be possible given the nature of the intervention.

#### Intervention group

Participants in the intervention group will receive an intensive education program delivered by a group of educators, researchers, and clinicians with expertise in tobacco control and tobacco dependence treatment. The program will be delivered at Qatar University over 4 days (run over two weekends) with an average of eight contact hours per day (i.e., approximately 32 contact hours). The program will target the Core Competencies for Evidence-based Treatment of Tobacco Dependence by the Association for the Treatment of Tobacco use and Dependence (ATTUD) [28].

The training curriculum will cover the following topics:Tobacco-use epidemiology in Qatar and globallyRisks and consequences of tobacco useBenefits of quitting tobacco usePrinciples of nicotine addictionRole of pharmacist in implementing tobacco-cessation interventionsTranstheoretical model (TTM) for behavior change as applied to tobacco-use cessationApplication of the TTM to provide tobacco cessation targeted to the patient’s readiness to changeBehavioral modification techniques for tobacco cessationUse of NRT including: indications, the choice of dosage form, dosing regimen, duration of therapy, adverse effects, precautions, contraindications, tapering, pharmacokinetic and pharmacodynamic drug interactions, and patient counseling pointsPharmacist and patient information on NRT and other cessation aidsUse of alternative medications (varenicline, bupropion, etc.) and modalities for cessation of tobacco useNicotine withdrawal symptomsGeneral verbal and nonverbal communication skillsPatient counseling and interviewing techniques including the ABC (ask, brief advice, cessation treatment) smoking cessation strategy and the 5A’s counseling process (ask, advise, assess, assist, and arrange)Development of a personalized action plan to assist the patient with smoking cessationDocumentation in the patient profileTobacco use and cessation in special populations (e.g., young patients, elderly, pregnant women, and others)

The program will be provided through didactic lectures and through active learning strategies including problem-based learning (PBL) exercises using case scenarios, group discussions, games, role plays, videos, simulated practical applications with peers and standardized patients, self and peer debriefing and performance feedback activities. At the end of the program, the pharmacists will be provided with a video recording of all the program content, copies of tools that they can implement in practice and information on online resources containing additional tobacco-cessation-related content. They will also be encouraged to contact the research team at any time if they have any questions or concerns. At the conclusion of the training program, all the pharmacists in the intervention group will receive continuous education (CE) units accredited by Qatar Council for Healthcare Practitioners (QCHP) of the Qatar Ministry of Public Health.

#### Control group

A short didactic session on a non-tobacco-related topic will be delivered at Qatar University to pharmacists in the control group to avoid contaminating this group with elements that could change their behavior and shift it to another level not representative of their tobacco-cessation-related “current practice” or “usual care.” Pharmacists in the control group will also receive CE units accredited by Qatar Council for Healthcare Practitioners (QCHP) of the Qatar Ministry of Public Health. Examples of potential topics that will be covered in the control group are in relation to women’s health such as contraception.

### Outcome measures

The study has two primary outcomes: post-intervention tobacco-related knowledge and post-intervention skills for tobacco cessation assessed using a multiple-choice-based evaluation instrument and an OSCE, respectively. The secondary study outcomes are post-intervention attitudes towards tobacco cessation and self-efficacy in tobacco-cessation interventions assessed using a survey instrument. An additional secondary study outcome is the post-intervention performance difference in relation to tobacco-cessation skills in the practice setting assessed using the simulated client approach.

### Pre- and post-program assessment of pharmacists’ knowledge, attitudes, and self-efficacy

#### Study procedures

This evaluation of the program effectiveness will utilize a before-and-after design between the two groups. The 4-day education program for tobacco treatment will serve as the intervention. Pre-tested instruments will be used to assess knowledge, attitudes and perceived self-efficacy (i.e., confidence) among intervention participants and control participants before and after the program.

#### Setting

This evaluation will be conducted in the same venue as the training program (i.e., Qatar University).

#### Assessment implementation

The assessment instruments will be distributed to participants in both groups prior to, and following, the program. The assessment will be likely online using a survey software. Participants will be allowed a certain predetermined time to complete the evaluations. Unique participants’ codes will be created to link the pre to post data for the same participant.

### Post-program assessment of pharmacists’ skills using the OSCE

#### Design and structure of the OSCE

Effective provision of tobacco-cessation intervention requires significant amount of skills in addition to the relevant knowledge. The proposed program has been carefully designed to cover a set of skills and competencies. Assessing participants’ practical skills using the traditional assessment methods (e.g., multiple choice questions (MCQs) or short essay) may not be appropriate in assessing skills associated with tobacco cessation An alternative means to assess a pharmacist’s practical skills in the delivery of effective tobacco cessation is the use of an authentic, performance-based assessments, such as the OSCE. Examples of skills to be assessed include communication skills in general, counseling skills, professional practice and ethics, and interviewing skills. We propose a five- to eight-station OSCE that will target core competencies and skills covered in the program. Participants in both groups will do the OSCE. In the OSCE, each participant will be allocated 10 min to interact with a standardized patient (SP) who will be trained using a validated script. Performance of participants will be assessed using validated assessment checklists. The cases and the assessment checklists will be reviewed for content and face validity by at least two faculty members who have expertise in tobacco cessation and suggested changes will be incorporated. Assessors for each station will be trained on using the checklists and will be blinded in relation to the study participants’ groups. The OSCE will be conducted in the same venue as the training program.

### Three- to six-month post-program assessment of pharmacists’ skills using simulated client approach

In this phase, the study will evaluate whether participants in the intervention and control groups will offer appropriate tobacco-cessation counseling and will recommend proper tobacco-cessation aids in their practice setting. Using a simulated client approach to data collection 3 to 6 months post training program, the study will assess the appropriateness of advice and recommendations given to a simulated client who asks for assistance in quitting smoking. The simulated client method is recognized and used internationally for assessing the quality of services offered by pharmacists including smoking cessation [29–32]. Simulated clients using two designed and validated case scenarios will visit participants in both groups. The clients will be selected to resemble the sociodemographic and practice characteristics of the Qatar population and its residents. Objective assessment forms will be developed using tobacco-cessation guidelines including the U.S. Department of Health and Human Service clinical practice guidelines (CPGs) for treating tobacco use and dependence and the Qatar guidelines for management of tobacco dependence as guides [5, 33]. Individual items in assessment forms will be completed using dichotomous scales (closed-ended yes/no questions) and will target different aspects of pharmacist performance including gathering information and patient history-taking, assessing the patient, recommending an appropriate treatment plan, and providing counseling. Research assistants will accompany the simulated clients in their visits. They will complete the assessment forms and will record the notes summarizing the encounter. One-to-one training will be provided to simulated clients and RAs by the study research team. Training will offer opportunities for the shoppers to role-play and to become proficient in their assigned scenarios, will help in refining the assessment sheets, in standardizing the process for all participants and in decreasing inter-rater variability. Both simulated clients and RAs will be blinded for the pharmacist group allocation. Each simulated client will enter the community pharmacy and will ask to speak to the pharmacist. The client will start with designed queries as per an assigned scenario. The pharmacist will then be given the chance to offer the counseling. After the visit is completed, an explanation of the purpose of the visit and how the collected data will be de-identified will be shared with the pharmacists. Anonymity and confidentiality will be ensured. Consent to participate in this phase of the study will be sought at this time. For pharmacists who decline to participate, information collected during the patient encounter will be discarded.

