### Statistical analysis

Data will be analyzed using IBM SPSS (IBM SPSS® for Windows, Version 24.0; IBM Corp, Armonk, NY, USA). The Consolidated Standards of Reporting Trials (CONSORT) guidelines will be followed when analyzing the study data [34]. Demographic and other pharmacist education and practice-related questions, along with baseline knowledge, attitudes, and perceived self-efficacy, will be summarized using means and standard deviations for numeric variables such as age and year of experience and frequency distribution for categorical variables such as gender, country of education, etc. Those will be compared between the study groups so that differences will be used to adjust the primary analyses.

The primary analyses will include comparing post-knowledge scores between the two study arms using the independent *t* test and the skills-related scores on the OSCE using the same method. The secondary analyses will include adjusting the main analyses to any imbalances in baseline variables that are observed between the study arms. This will be done using the linear regression method. Moreover, knowledge scores will be compared within each study group using the paired *t* test. For outcomes that are dichotomous or that will be dichotomized, such as the percentage of pharmacists with a specific attitude or self-perceived efficacy, then the chi-squared test will be used to compare such outcomes between study groups and the McNemar test will be used to compare responses within each study group over time. Performance on the simulated patient will be compared in a similar manner as the outcomes above depending on whether it is dichotomized or not. In addition, repeated-measures analysis (depending on the scale of measurement for each outcome) may be used to detect whether there is an intervention × time interaction so that difference between study groups is changing over time or not. The level of statistical significance will be set at 5%.

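### The simulated-client comparison uses two scenarios but no scenario term, which costs some precision on the only outcome measured in practice

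*Protocol article*

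**What the plan says.** The practice-setting assessment is described in the section on the three- to six-month simulated-client visits. Two scenarios are used: "Simulated clients using two designed and validated case scenarios will visit participants in both groups". Within a visit, "The client will start with designed queries as per an assigned scenario". On scoring: "Research assistants will accompany the simulated clients in their visits. They will complete the assessment forms"; the forms consist of yes/no items. Clients and research assistants receive one-to-one training, which is meant to help "in standardizing the process for all participants and in decreasing inter-rater variability". On masking: "Both simulated clients and RAs will be blinded for the pharmacist group allocation". Once the visit is over, its purpose is explained to the pharmacist and consent for this phase is sought. The data of those who decline are discarded.

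The article does not state how many visits each pharmacist receives, how a scenario is assigned to a visit, or how many observers there are.

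On analysis, the Statistical analysis section says: "Performance on the simulated patient will be compared in a similar manner as the outcomes above depending on whether it is dichotomized or not". The outcomes above that sentence are compared between arms by the independent t test or the chi-squared test. The only adjustment named is "adjusting the main analyses to any imbalances in baseline variables that are observed between the study arms", by linear regression. The Outcome measures section lists simulated-client performance as a secondary outcome.

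**The concern.** Scenario is a known feature of the design, fixed before any data are collected, and it may well affect the score: two validated cases need not be equally hard. The named test has no place for it. The planned adjustment does not cover it either, because it is triggered by imbalance in baseline variables, and the scenario used at a visit months after training is not one. The optional repeated-measures analysis looks at intervention by time, not at scenario.

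Any difference in difficulty therefore goes into the error term. At stake is the sensitivity of the one outcome that shows whether trained skills carry over to the pharmacy counter. Allotment can be arranged only before the visits; once they are done, only the model term remains.

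**Working it through.** **The plan's own figure.** The Sample size estimates section gives 54 per group for 80% power at an effect of 0.60 SD. A two-sided independent t test at 0.025 reproduces it: the exact solution is 54.08 per group, with 79.9% power at 54. (The level is printed as 0.025%, which would need 113 per group; I read it as 0.025.) Allowing for 10% loss, 54/0.90 = 60. No calculation is given for the simulated-client score. At the 5% level that the Statistical analysis section sets, 54 per group gives 80% power for an effect of 0.544 SD.

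**Assumptions, none from the documents.** One visit per pharmacist; half the visits on each scenario, assigned independently of arm; a true effect of 0.55 within-scenario SD; a scenario gap g of 0.25, 0.5 or 1.0 within-scenario SD; a continuous score.

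**Error SD when scenario is ignored.** A 50:50 mix of two scenarios that differ by g adds g²/4 to the variance, so the SD is √(1 + g²/4). The effect seen by the plain test is 0.55 divided by this.

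| g | Error SD | Effective effect | Power, scenario ignored | 54 per arm is worth |
|---|---|---|---|---|
| 0 | 1.000 | 0.550 | 80.8% | 54.0 |
| 0.25 | 1.008 | 0.546 | 80.2% | 54/1.0156 = 53.2 |
| 0.5 | 1.031 | 0.534 | 78.4% | 54/1.0625 = 50.8 |
| 1.0 | 1.118 | 0.492 | 71.7% | 54/1.25 = 43.2 |

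With scenario in the model, power returns to about 80.8%, ignoring the degree of freedom spent. The loss is 0.6, 2.4 and 9.1 percentage points.

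**Validity.** In simulations of 5,000 trials each, with scenario (and, in some runs, observer) assigned independently of arm, the type I error of the plain t test lay between 4.6% and 5.5%.

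**Chance imbalance.** The difference between arms in the share of visits on one scenario has SD √(2 × 0.25/54) = 0.096. Its 95% effect on the estimate is therefore ±1.96 × 0.096 × g, or ±0.05, ±0.09 and ±0.19 SD for the three gaps. The corresponding variance is g² × 2 × 0.25/54 = (2/54) × g²/4, which is exactly the scenario part of the variance used in the table. It is the same loss in other units and must not be added to it.

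**If each pharmacist meets both scenarios.** Scenario difficulty then cancels between arms. Treating the two visits as independent records would, however, raise the simulated type I error to about 7% at an assumed within-pharmacist correlation of 0.2 and about 11% at 0.5.

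**Observers.** Observer severity would enter the error term in the same way as scenario. Neither the number of observers nor their spread is given, so I attach no headline figure to it.

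**The case against.** The strongest objection is that this is a journal article. It says that scenarios are assigned, so a scheme presumably exists, and visit rosters and model terms are commonly left to the full protocol or analysis plan. The article also states real safeguards: validated scenarios, objective yes/no forms, training, and blinding of clients and observers. At a gap of 0.25 SD the loss is under one point of power, and the outcome is secondary.

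Much of this stands. The missing roster alone would not be a point, and training should shrink observer differences. What remains is that the article does name a test, and a nearly free alternative is more precise for the data collection described. Validation does not make two cases equally hard.

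A reader might go further, in three ways that the documents do not support:

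- **That the comparison is biased.** Blinded staff who assign scenarios without regard to arm leave the estimate unbiased, and they can alternate scenarios or rotate observers without knowing the arm. Distortion needs scenarios or observers tied to arm, which the article nowhere says.
- **That chance imbalance is a further harm** on top of the lost power. It is the same variance, already inside the standard error of the t test.
- **That several client and observer pairs are known to be in use.** This rests only on plural nouns.

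One visit per pharmacist is itself a reading. Disclosure after the visit makes it the better one, since a second visit would no longer be covert, but the text does not settle it.

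**Conclusion.** The point holds as a modest loss of precision on a secondary outcome. The named test is valid if scenario assignment is independent of arm, but it is less efficient than it could be. At 54 per arm and a 5% level the cost is about 1 to 9 points of power for scenario gaps of 0.25 to 1.0 SD. That range rests on an assumed gap, an assumed effect of 0.55 SD and one visit per pharmacist, and it applies to the score; I did not size the yes/no version. If both scenarios are used for each pharmacist, the scenario loss disappears and the question becomes how the two visits are combined.

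**What to change.** Before the visits begin:

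1. State the number of visits per pharmacist.
2. Have the study statistician issue a visit list, without arm labels, that allots the two scenarios in equal numbers within each arm. Rotate observers across arms.
3. Replace the plain test by linear regression of the score on arm and scenario. For a yes/no result, use a Mantel-Haenszel analysis stratified by scenario, or logistic regression with both factors. Add observer as a factor only if there are few observers.
4. If a pharmacist meets both scenarios, analyse one averaged score per pharmacist.

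The list and the model term belong together. With a balanced list and a plain test, the standard error would still contain the scenario variance and be too large. A balanced list can also end up unbalanced, because data from pharmacists who decline consent after the visit are discarded.

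The cost is one list, one or a few degrees of freedom, and slightly less flexible scheduling.
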